**Objective:**

The objective of the ECHO study is to investigate the impact of maternal E-cigarette use during pregnancy on obstetric, neonatal, and infant outcomes.

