### Population

This prospective, multicentre, observational cohort will focus on women pregnant with a singleton fetus who self-report vaping, cigarette smoking, vaping and cigarettes smoking, or no exposure (controls). The obstetric portion of the study operates from three recruitment sites; The Coombe Hospital, The Rotunda Hospital, and the National Maternity Hospital—these standalone maternity units, based in Dublin, Ireland’s capital city, cumulatively deliver approximately 22,000 women annually [31–34].

Smoking and vaping patterns will be assessed using a combination of digital validated patient questionnaires administered at set timepoints throughout pregnancy, in addition to objective assessment of exhaled breath carbon monoxide (BCO) assessed by point of care exhaled carbon monoxide breathalysers (Bedfont’s ‘Smokerlyzer’® device) at each antenatal study visit. Nicotine levels will be assessed using quantitative urinary cotinine, analysed by Eurofins Biomnis enzyme immunoassay.

Women are recruited prior to 24-week gestation after being directly asked about smoking and vaping status in a structured fashion at their booking visit; if they fulfil the eligibility criteria, they are then invited to partake in the study as either a vaper, a smoker, a smoker/vaper or a control (Table 1.).

**Table 1 Tab1:** Exposure status

Vaper	Vaper/smoker	Smoker	Control
• Reports vape use • BCO ≤4 ppm	• Reports dual use • BCO ≥ 5 ppm	• Reports cigarette smoking • BCO ≥ 5 ppm	• Denies cigarette smoking or vaping • BCO ≤4 ppm

A BCO measurement of ≥ 5 parts per million (ppm) was selected to define active smoking, in keeping with Irish National Clinical Guidance. Selection of BCO ≥ 5 ppm as a cutoff confers a sensitivity of 0.9 and specificity of 0.92 [35]. This is an important consideration in accurately classifying both smokers and smoker/vapers in addition to self-reported exposure status.

After screening, demographic and biometric data points are gathered, and a series of questionnaires are administered digitally as per the schedule outlined below:

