### Obstetric secondary outcomes

Trends in smoking cessation and crossover from smoking to vaping and from vaping to non-smoking/non-vaping/smoking.BCO at screening, 20 weeks, third trimester, and postnatally.Quantitative urine cotinine assay in the third trimester.Estimated fetal weight (EFW)—using the Hadlock formula [41]—fetal and maternal dopplers at 20 weeks and 32–34+6 (maternal: uterine artery Doppler, fetal: umbilical artery, middle cerebral artery, cerebroplacental ratio).Incidence of small for gestational age (SGA) defined as EFW and/or AC less than the 10th centile for gestational age on ultrasound at any gestation after study entry.Diagnosis of congenital malformation.Birth centile [42].Blood pressure measurement at screening, 20 weeks and third trimester, and postnatally.Incidence of essential hypertension—high blood pressure at booking defined at a BP 140/90 mmHg.Incidence of diagnosis of pregnancy-induced hypertension and incidence pre-eclampsia [43].Incidence of pre-labour premature rupture of membranes (PPROM).Incidence of anaemia, defined as a haemoglobin level of less than 10g/dL at booking, 28 weeks or any other time point in the antenatal period.Maternal history of abnormal cervical screening cytology or cervical surgery.Indication for and incidence of induction of labour.Mode of delivery.Delivery complications.Incidence of postnatal caesarean, episiotomy or perineal wound infection requiring antibiotics.Edinburgh Postnatal Depression Scores prior to discharge.Incidence of venous thromboembolic (VTE) disease—new onset deep venous thrombosis or pulmonary embolus.Unscheduled admission to hospital.Admission to high dependency unit (HDU) or inter-hospital transfer to intensive care unit.

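### Two obstetric secondary outcomes are already fixed at or before cohort entry, and the anaemia incidence pools booking cases with later onset

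*Protocol article*

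**What the plan says.** The Abstract states the aim as "to investigate the impact of maternal E-cigarette use during pregnancy on obstetric, neonatal, and infant outcomes". On cohort entry, Population says: "Women are recruited prior to 24-week gestation after being directly asked about smoking and vaping status in a structured fashion at their booking visit".

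Under Obstetric secondary outcomes the article lists, among others:

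- "Maternal history of abnormal cervical screening cytology or cervical surgery"
- "Incidence of essential hypertension—high blood pressure at booking defined at a BP 140/90 mmHg"
- "Incidence of anaemia, defined as a haemoglobin level of less than 10g/dL at booking, 28 weeks or any other time point", which the article extends to the whole antenatal period.

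The same list limits small for gestational age to findings "on ultrasound at any gestation after study entry" and limits venous thromboembolism to new cases. Demographic and baseline disease characteristics says that past obstetric and gynaecological history is taken from the booking assessment. Sample size and planned statistical analyses says in general terms that potential confounders or modifiers will enter the models, and names none. Exclusion criteria removes women with a history of significant medical disease, without defining significant.

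**The concern.** An outcome in a cohort should be able to arise after entry. A past cervical history cannot. Hypertension defined by the booking reading is a status at entry, although it is labelled an incidence. Anaemia can arise after entry, but the definition also counts women already anaemic when they joined.

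Vaping and smoking are self-selected, so the groups may well differ in earlier health. If the definitions are followed as written, such differences appear in the outcome tables of a study whose aim is the impact of e-cigarette use in pregnancy. The anaemia comparison blends prevalent with new cases, so its odds ratio describes neither. The Dissemination section expects the findings to inform guidelines, so the labelling matters.

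**Working it through.** **1. Timing of each definition against cohort entry (at or after booking, before 24 weeks)**

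| Item | When it is determined | Can a new case arise after entry under the definition? |
|---|---|---|
| Cervical cytology or surgery history | Before entry, by its wording | No |
| Essential hypertension | At booking | No |
| Anaemia | Booking, 28 weeks or any other antenatal time | Yes, but booking cases are also counted |
| Small for gestational age | After study entry | Yes, and only then |
| Venous thromboembolism | New onset | Yes, and only then |

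The last two rows show that the authors apply the new-case restriction where they intend it. The baseline section already covers gynaecological history, so cervical history stands as both a baseline item and an outcome. No sentence marks the three items as descriptive.

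**2. How often a prior imbalance would look like a finding**

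The documents give no rates for these items, so there is no figure of the plan's to reproduce. What follows is an illustration. From the article: 400 per group, type I error 0.05 (taken as two-sided) and an uncorrected chi-square test. Assumed: prevalence p0 in controls, prior odds ratio OR in vapers, and no effect of vaping in pregnancy.

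- p1 = OR·p0/(1−p0) ÷ [1 + OR·p0/(1−p0)]
- SE0 = √[2·p̄(1−p̄)/n], with p̄ the mean of p0 and p1
- SE1 = √{[p0(1−p0) + p1(1−p1)]/n}
- Chance of significance = Φ[(p1 − p0 − 1.96·SE0)/SE1]

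Example with p0 = 0.10 and OR = 1.5: p1 = 0.143, SE0 = 0.0231, SE1 = 0.0230, so Φ[(0.0429 − 0.0453)/0.0230] = Φ(−0.105) = 0.46.

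| Prevalence in controls | Prior OR 1.5 | Prior OR 2.0 |
|---|---|---|
| 5% | 28% | 69% |
| 10% | 46% | 92% |
| 15% | 59% | 97% |

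The nominal rate is 5%.

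**3. Anaemia**

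Assumed: booking prevalence b of 2–5% in controls, prior OR 2, and the same new-onset risk i of 5–10% in both groups. The pooled risk in each group is b + (1−b)·i.

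Example with b = 5% and i = 5%: controls 0.05 + 0.95 × 0.05 = 0.0975. In vapers the booking prevalence is 0.0952, giving 0.0952 + 0.9048 × 0.05 = 0.1405. The pooled odds ratio is (0.1405/0.8595) ÷ (0.0975/0.9025) = 1.51, although the odds ratio for new onset is 1.

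Over the four combinations of b and i the pooled odds ratio runs from 1.17 to 1.51, and the chance of significance from 11% to 47%. With a prior OR of 1.5 the ranges are 1.08–1.26 and 6–17%.

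**4. Denominator after the fix**

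Under the prior OR 2 assumptions, controls fall from 400 to 392 (b = 2%) or 380 (b = 5%). Vapers fall to 400 × (1 − 0.0392) ≈ 384 or 400 × (1 − 0.0952) ≈ 362.

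**The case against.** The strongest reply is that this is labelling. The list works partly as a data inventory: breath carbon monoxide at screening and urine cotinine, which are exposure measures, appear in it too. The stated hypotheses concern preterm birth, birth weight, neuro-behaviour and respiratory symptoms, and none concerns these three items. That the authors would interpret them causally is an inference. This is fair, and it limits the weight of the point. It does not remove it, because the items stand under an outcomes heading, two are called incidences, and neighbouring items carry the restriction that these lack.

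A reader might infer several stronger things that the documents do not support:

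- **All three conditions precede exposure.** Booking falls within pregnancy and may be as late as 24+0 weeks, so booking blood pressure and haemoglobin may follow some vaping in pregnancy. Only cervical history is safely prior. The cohort cannot separate early exposure from prior difference, so booking values are still not incident after entry. Anaemia is not complete at booking.
- **The exclusion criterion empties the hypertension outcome.** A first raised reading at booking need not be a history, nor mild hypertension significant. The two statements sit awkwardly together, but no more is shown.
- **Women hypertensive at booking contaminate the denominator for pregnancy-induced hypertension.** The article does not state that denominator. It cites a source not at hand, and such detail may sit in the full protocol.
- **Preterm birth is left confounded because cervical surgery is listed as an outcome.** The general adjustment statement and the collection of gynaecological history at booking leave it available as a covariate. Naming covariates is commonly left to the analysis plan.

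**Conclusion.** The point holds for the definitions as written. Cervical history and booking hypertension are fixed at or before entry and belong at baseline. The anaemia incidence mixes prevalent with new cases and is only partly at fault. General covariate adjustment does not cure this, since it cannot turn a past history into an outcome.

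The size cannot be taken from the documents. The illustrative figures rest wholly on assumed prevalences and prior odds ratios. They show that a modest prior imbalance would often reach significance for the first two items and would distort anaemia less. The primary outcomes and the sample size do not depend on these items. It is a correction worth making, confined to secondary outcomes.

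**What to change.** - Move cervical history and hypertension at booking from the outcome list to baseline characteristics. Both remain available as covariates under the existing adjustment statement.
- Report anaemia at booking as a baseline characteristic. Count incident anaemia, with the existing haemoglobin threshold, at 28 weeks or any other antenatal time after entry, among women not anaemic at booking. Limiting it to the 28-week test would lose later cases that the present definition captures.
- Reconcile the essential hypertension item with the exclusion for significant medical history, so that a reader can tell which women with raised booking pressure are in the cohort.
- Do not make adjustment for booking blood pressure mandatory. It may be measured after exposure has begun and so lie on the causal path; its use needs a stated rationale.

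The items needed are already in the plan, so no new collection is required. The cost is rewording and a smaller anaemia denominator: about 8–20 fewer controls and 16–38 fewer vapers out of 400 under the assumptions used above.

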### Secondary neonatal outcomes

APGAR scores at 1 and 5 minutes.Brazelton’s Neonatal Behavioural Assessment Scale (NBAS).Umbilical artery blood gas (if available).Admission to neonatal intensive care (NICU) or special care baby unit (SCBU).Incidence of neonatal hypoglycaemia as per local guidelines.Incidence of neonatal jaundice requiring phototherapy.Mode and type of infant feeding.Neonatal anthropometric measurements (weight in grams, length, head, chest and waist circumference in centimetres).A subgroup of 150 infants will have PEAPOD assessment. The PEAPOD is a specialised scale that both weighs a baby and uses air displacement plethysmography to determine the baby’s body volume. These measurements allow us to calculate the baby’s density and estimate the baby’s body fat and lean body mass [41].

### Paediatric secondary outcomes

Paediatric anthropometric measurements (weight, height, body mass index, head circumference, waist circumference, chest circumference and mid-arm circumference measurements) at 12 and 24 months.Episodes of wheeze, bronchiolitis, pneumonia and ENT infections and/or wheeze at 6, 12 and 24 months.Frequency, timing and intensity of wheezing episodes.Prescribed respiratory medications.Diagnosis of eczema.Number of attendances/admissions to hospital.

### Neurocognitive and psychological secondary outcomes

Early Executive Functions Questionnaire (EEFQ) at 12 and 24 months.Infant Behaviour Questionnaire (IBQ) at 12 months.Child Behaviour Checklist (CBCL) at 24 months.A subgroup of 150 infants will have a Bayley Scales of Infant and Toddler Development assessment performed at 12 months of age.*Maternal* Barkley Functional Impairment Score at infant 1 year visit.Edinburgh Postnatal Depression Score at birth and penultimate study visit.

### Study duration

The anticipated duration of the study is 48 months, with an active recruitment period of 15–18 months.

### Sample size and planned statistical analyses

We will aim to achieve as representative as sample as possible of each population. Descriptive statistics on outcomes and other risk factors will be derived for the three groups at each timepoint. An assessment of representativeness of each group will be made based on baseline indicators. In the case that key measurements are missing at rates in excess of 5%, multiple imputation procedures will be considered. Longitudinal analyses of the outcomes will be conducted using (normal or logistic) multilevel (mixed effects) models to account for repeated measurements within individuals. Generalised additive models (GAMs) or logistic GAMs (lGAM) will be used to estimate group differences in each outcome over time in a fully flexible model that can allow for non-linear change without overfitting. Potential confounders or modifiers of the outcomes will be incorporated into the models as predictors or by utilising interaction terms as appropriate.

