## Outcomes

### Primary outcomes

The primary outcomes outlined in Table 2 have informed the sample size calculation. As the outcomes for the postnatal psychological assessments are exploratory, we have used a pragmatic sample target of 150.

**Table 2. Tab2:** Primary outcomes

Primary outcomes		
Obstetrics/neonatal	Paediatrics	Psychology
• Preterm birth • Low birth weight	• Doctor-diagnosed wheeze	• Neonatal Behavioural Assessment Scale • Bayley’s Infant and Toddler Development (*n*=150)

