**Table Taba:** 

Women who vape during pregnancy will be more likely have a preterm birth and that their infants will have a lower birth weight (LBW), lower neuro-behavioural scores and increased respiratory symptoms when compared with non-smokers.
Women who vape during pregnancy will be less likely to have a preterm birth and their infants will have a higher birth weight, higher neuro-behavioural scores, and fewer respiratory symptoms than when compared with tobacco smokers.

The best available data suggest a prevalence of smoking rate during pregnancy in Ireland is between 9 and 10% [44], whilst the current expected rate of vaping during pregnancy is approximately 5% [45]. The cumulative live birth rates in the three maternity hospitals in Dublin in 2023 were: The Coombe Hospital—6974, The Rotunda Hospital—8442, and the National Maternity Hospital—6880, which will give a projected denominator of approximately 22,000 total live births. The incidence of vaping during pregnancy in the Coombe is 5% [34, 46]; projected to the other three hospitals gives approximately 750–1250 vapers per annum. The calculations in Table 3 give the magnitude of a detectable association with (2-year) prevalence of each condition (odds ratios) or mean differences that are detectable at a power of 80%, with a type I error rate of 0.05. These assume use of simple uncorrected Chi-square test or *t* tests. Detectable effect sizes are presented assuming a range of sample sizes to illustrate how power is maintained under a range of recruitment scenarios. We plan to collect three equally sized groups—non-smokers, smokers, and vapers

**Table 3 Tab3:** Sample size calculation

Sample size (per group)	Baseline incidence		
	10% (wheeze)	6.2% (preterm birth)	5% (low birth weight)
	Detectable odds ratios:		
100	3.00	3.62	3.19
200	2.25	2.63	2.26
300	1.96	2.24	1.91
**400**	**1.80**	**2.04**	**1.74**

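### The longitudinal models named (normal or logistic) do not suit the paediatric event counts, which come from unequally spaced questionnaires; a rate model and a stated recall period would be better (minor)

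*Protocol article*

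**What the plan says.** Under *Sample size and planned statistical analyses*, the protocol article states: "Longitudinal analyses of the outcomes will be conducted using (normal or logistic) multilevel (mixed effects) models to account for repeated measurements within individuals". The next sentence reads: "Generalised additive models (GAMs) or logistic GAMs (lGAM) will be used to estimate group differences in each outcome over time". Neither sentence makes an exception for counts. The mixed models are therefore limited to two families. The distribution of the plain GAM is left open.

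*Paediatric secondary outcomes* lists "Episodes of wheeze, bronchiolitis, pneumonia and ENT infections and/or wheeze at 6, 12 and 24 months", then "Frequency, timing and intensity of wheezing episodes" and "Number of attendances/admissions to hospital". Only the first of these carries timepoints. *Sequence of questionnaire timepoints* places the postnatal questionnaires after birth and at 6 months, 1 year and 2 years. No section says what period each questionnaire asks about.

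The primary paediatric outcome in Table 2 is "Doctor-diagnosed wheeze", which is binary and is not part of this point.

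**The concern.** Attendances, admissions and wheezing frequency are counts, and neither named mixed-model family is a count model. A normal model describes skewed counts with many zeros poorly. A logistic model reduces them to any versus none and loses the frequency that the outcome asks for. This mismatch does not depend on how the questionnaires are worded.

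A second problem depends on the recall period. The gaps between postnatal questionnaires are 6, 6 and 12 months. If each report covers the time since the last one, the third count accumulates over twice as many months. On the absolute scale, a group difference that is constant per month then looks twice as large in the second year. The GAMs are meant to estimate group differences over time, and respiratory symptoms appear in both study hypotheses. An apparent widening with age could be read as a growing effect of vaping or smoking.

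**Working it through.** **The plan's nearest figure.** The article gives no power figure for episode counts or attendances. The nearest is Table 3 for wheeze: a detectable odds ratio of 1.80 at 400 per group and 10% baseline, "detectable at a power of 80%, with a type I error rate of 0.05". A pooled two-sided chi-square calculation without continuity correction gives 2.99, 2.25, 1.96 and 1.81 for 100, 200, 300 and 400 per group, against the stated 3.00, 2.25, 1.96 and 1.80. The wheeze column reproduces, and it rests on a binary outcome, so this point leaves it unchanged.

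**Inputs.** From the article: questionnaires at 6, 12 and 24 months, 400 per group, wheeze about 10%. Assumed: windows, event rates, rate ratio and frailty. The 10% is taken as a two-year figure, as the power section does; the text below Table 3 gives it for the first 3 years, which would make the rate lower and the distortion smaller.

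**Expected difference under a normal-type model on raw counts.** With control rate λ per month, rate ratio RR and a window of w months, the difference in mean counts is λ × w × (RR − 1).

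- λ = 0.10, RR = 1.3, windows 6/6/12: 0.18, 0.18, 0.36. Dividing by w gives 0.03 per month each time.
- 10% in two years, λ = −ln(0.9)/24 = 0.00439, RR = 1.8: 0.021, 0.021, 0.042, or 0.0035 per month each time.
- Counts cumulative from birth (6, 12, 24 months), λ = 0.10, RR = 1.3: 0.18, 0.36, 0.72, a ratio of 1:2:4.
- Equal recall of 6 months each time: 0.18, 0.18, 0.18. There is no distortion, but months 12 to 18 are unobserved (6/24 = 25%).

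**Logistic model for any episode.** Without frailty, P = 1 − exp(−λw). With 10% in two years and RR = 1.8, the odds ratios are 1.82, 1.82 and 1.84. Over two-year incidences of 10% to 50% and RR from 1.3 to 2.0, the odds ratio rises from the 6-month to the 12-month window by a factor of 1.00 to 1.10 (largest: 2.414/2.189 = 1.10). With gamma frailty of variance 1, P(no event) = 1/(1 + λw), so the odds of any event are λw. The marginal odds ratio then equals RR in every window.

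**False finding of a changing effect.** Simulated Poisson counts with gamma frailty (variance 1), 400 per group, constant RR = 1.3, windows 6/6/12. The group test is applied to [count in months 12–24] minus the mean of the two 6-month counts.

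| Control rate | Controls with any event by 24 months | Rejection, raw counts |
|---|---|---|
| about 10% in two years | about 10% | about 7% |
| 0.03 per month | 1 − 1/1.72 = 42% | 18% |
| 0.05 per month | 1 − 1/2.2 = 55% | 26% |
| 0.10 per month | 1 − 1/3.4 = 71% | 43% |

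Repeat runs gave 7–8%, 15–18%, 24–26% and 38–43%. With events per month as the response, rejection stayed at about 5% throughout.

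**The case against.** The strongest case against is that this is a condensed journal article, with one general paragraph covering many outcomes. An offset, a link function and a recall period for secondary outcomes are commonly left to the full protocol or SAP. That stands: the missing offset is not in itself an error. It does not dispose of the point, because the article does name families for the outcomes generally, and those families do not fit counts.

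A reader might infer that the counts do come from windows of 6, 6 and 12 months, and that the planned analysis will therefore show an effect doubling in the second year. The documents do not support this. The windows are inferred from visit spacing, and attendances and wheezing frequency have no timepoint at all. Doubling needs three things together: recall since the last questionnaire, raw counts, and a normal-type model. The article does not commit to that combination, and it does not rule out analysing events per month. Nor does the doubling carry over to the logistic option.

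It would also be too strong to say that only normal or logistic models are allowed, since the plain GAM has no stated distribution. The 43% is the high end of the assumed rates and implies 71% of control children affected by 24 months. At the only wheeze rate in the article, the excess over 5% is small. Infections and attendances may be commoner, but the article gives no rate for them.

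Finally, no stated hypothesis concerns an effect that changes between the first and second year. That also stands, although group differences over time are what the GAMs are said to estimate.

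**Conclusion.** The point holds in a limited form. The mixed-model families named do not match the count outcomes, whatever the recall period. The further distortion is conditional. Raw counts since the last questionnaire in a normal-type model double a constant absolute difference in the 12-month window; counts cumulative from birth give 1:2:4. The resulting false group-by-time rejection ranges from about 7% to 43% over the assumed rates, at a rate ratio of 1.3 and frailty variance 1. A logistic analysis of any episode is essentially free of this problem, at the price of discarding frequency.

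Priority is minor. Only paediatric secondary outcomes are affected; the primary wheeze outcome and every power and sample size figure are unchanged.

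**What to change.** For episodes, attendances and admissions, replace the normal or logistic family with a negative binomial mixed model, or a negative binomial GAM where a smooth time course is wanted. Use log(months covered by that child's report) as offset and report rate ratios. State the recall period of each questionnaire. Asking about the time since the previous completed questionnaire would leave no months unobserved. Any-wheeze outcomes can stay logistic.

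The cost is a change of wording, slightly more modelling, and rate ratios in place of mean differences. No extra participants or visits are needed. The offset requires the period covered by each report to be known; the article does not say whether completion dates are stored, so this should be confirmed.
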